#### Thematic analysis procedure for qualitative aspect

All audio-recordings from interviews and groups will be independently transcribed twice, once by the facilitator and once by a research assistant. Anticipated themes will be informed by the topic guides/interview schedules (feasibility, acceptability, impact, barriers, facilitators). Thematic content analysis will be done using Atlas.ti software (Additional file 1: Table S7).

### Sample size

It is believed that the within-group effects for both PE-A and SC in this study will be comparable to the effect sizes in previous studies examining these treatments in children and adolescents and adults [26, 36, 68, 69]. Using these data, it, is suggested that a total of 64 completers is necessary to provide 80% power for a two-tailed alpha level of 0.1. The literature suggests that as many as 30% of PTSD study entrants will terminate prematurely, i.e., drop out. A total of 90 entrants will thus result in 64 completers.

## Discussion

This is the first RCT using evidence-based CBT for PTSD in traumatized adolescents within a South African context. In addition, the study will be assessing the effectiveness of task shifting in a limited resource environment, using counsellors with minimal to no previous experience in psychosocial treatment of PTSD, which will be vitally important from a public mental health perspective. Should the results of this study demonstrate that PE-A is an effective psychotherapeutic intervention for treating symptoms of PTSD in adolescents exposed to trauma, when administered by trained counsellors, the implications for treatment recommendations may be wide-ranging. Thus, community-based personnel could be trained relatively easily to deliver the treatments within the sufferers’ environment, which in turn, would make effective treatments more readily accessible as well as more cost-effective.

### Potential risks

(i) Participants can develop mild to moderate emotional discomfort or frustration associated with interviewing, or completing lengthy questionnaires; (ii) participants may experience subjective distress during treatment; (iii) all participants are exposed to the risk of relapse during the non-treatment follow-up; and, d) participants might suffer from stigma at the schools they attend.

There is the risk that some participants accidentally state identifiable information on the recording device that is recognizable by the research assistant-transcriber.

During focus groups, (i) participants may experience mild emotional discomfort in situations where there are differences of opinion from theirs or (ii) when talking about aspects of treatment. (iii) Adolescents may be disappointed that they did not have the same therapeutic experience as another participant or (iv) they may fear being recognized by a fellow participant.

The risks for nurses is that they may experience anxiety concerning negative consequences in relation to voicing dissatisfaction about training and/or supervision conducted by the PI.

### Protection against risks

Participants not deemed study eligible (see exclusion criteria) or who themselves do not assent or their parents or guardians do not consent to participation in the study will be offered clinically appropriate treatment referrals outside the study.

Prior to exposure-based interventions, informed consent/assent will be obtained from eligible adolescent participants to reduce possible risks of mild to moderate anxiety when exposed to anxiety-provoking images and situations in treatment sessions, at home or doing homework. Each participant will be given a rationale for PE and advised of the procedure and the temporary effects that the procedure might have. Participants will be required to give assent prior to every exposure session or task. Exposure therapy has been shown to provide benefits. While some individuals fail to benefit from an intervention, very few report adverse effects. The exposure is individually titrated; in-vivo exposure starts with situations that elicit moderate anxiety and progress to more anxiety-provoking situations and triggers.

Risks associated with SC may include non-reduction of PTSD symptoms. All participants in this treatment condition who retain a PTSD diagnosis or manifest significant trauma-related symptoms, will be offered PE-A at the end of treatment.

In the nested qualitative study, to manage potential emotional risks, the focus groups and interviews will be conducted by a clinical psychologist. Participants will be encouraged to use code names while the recording is on and the recording will be identified by a code. Only the two transcribers will have access to the audio-recordings and transcribe using earphones in a private location. Transcribers will sign a confidentiality agreement. All identifiable information will be removed from the transcription prior to analysis. The PI will not be present during the focus group discussions and all feedback to him will be de-identified.

Adolescents will attend intervention specific (PE-A or SC) focus groups to protect them from exposure to an unfamiliar treatment experience. If there are enough interested adolescents, the groups can be further separated based on gender. Rules regarding confidentiality and respect will be reinforced throughout focus groups.

Participants’ reactions to study assessments and treatment will be closely monitored, and negative reactions will be addressed therapeutically. To avoid or reduce mild to moderate emotional discomfort or frustration associated with psychiatric interviewing or filling out questionnaires, adolescents and their parents will be allowed breaks as needed during in the assessment phases. Additionally, the intake assessment can be spaced over visits, if needed.

Participants in both conditions will be informed by their respective counsellors that they may call between sessions should they experience a crisis or are distressed enough to need psychological support. If a counsellor becomes concerned about a participant’s psychological welfare, contact will be made with the supervisor and PI who will arrange for psychological evaluation. Although unlikely, if substantial negative emotional reactions develop that require additional interventions, participants will be withdrawn from the study and referred to public health treatment providers to receive these services. Such identification can be made by IEs or study counselors, in consultation with the PI.

In cases where danger to self or others is identified, the adolescent will be withdrawn from the study and clinically appropriate emergency service procedures will be implemented. If previously undocumented sexual or physical abuse is discovered during consent or treatment, we will implement standard procedures for notifying the appropriate social services and provide referrals to local public mental health treatment centers. If a social work referral is required during treatment, the adolescent may or may not be continued in the study depending on what is in the best interest of the participant. This decision will be made by the PI and the treatment team in consultation with the adolescents’ primary caregiver, provided that this caregiver is not the perpetrator.

All study data will be confidential. The following steps will be taken to minimize risks to confidentiality: a) evaluation protocols and treatment record forms will be kept in locked cabinets in the IE office; b) participant identity will be disguised using ID numbers keyed to a master list; c) all recordings will be transferred to removable storage that will be kept in locked storage in locked rooms; d) data will be entered directly onto computer files that will be password protected; and e) computer files will carry only participant numbers for case identification. All project staff will be trained in the importance of confidentiality. If the results of the study are published, data that might reveal the identity of a participant will be disguised.

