## Objectives

### Research hypothesis

PE-A will be superior to SC as administered by counsellors in reducing PTSD symptoms at post-treatment as measured by the Child PTSD Symptom Scale – Interview (CPSS-I).PE-A treatment gains will be maintained at 3-, 6-, and 12-month follow-up and annually thereafter as measured by the CPSS-I

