**Fig. 1 Fig1:**
[figure not shown]
Study Consort Diagram, Consort diagram

A single-blind permuted block randomized control design will be used. The proposed research aims to examine the effectiveness of a psychotherapeutic intervention administered by counsellors to treat the symptoms of PTSD in adolescents exposed to trauma. The aim is to conduct a randomized controlled trial (RCT) to compare PE-A to SC to determine the comparative effectiveness in reducing PTSD and associated symptoms in adolescents.

The study will compare the efficacy of PE-A to SC. Participation will be voluntary. All participants, who meet full PTSD or sub-threshold PTSD criteria, will be scheduled for a pre-treatment assessment with Independent Evaluators (IE). The one IE will be an experienced diagnostician and clinical psychologist and the other an experienced psychiatric nurse. Adolescents will be randomly assigned on a 1:1 ratio to receive either PE-A or SC.

Treatment will consist of 7–14 sessions of either PE or SC. The number of sessions each participant receives will be based on the weekly self-report measure of PTSD symptoms (Child PTSD Symptom Scale – Self Report; CPSS-SR); however, this will range between a minimum of 7 sessions to a maximum of 14 sessions. A 70% symptom reduction is chosen as sufficient for treatment termination.

After session five, all participants will receive a mid-treatment evaluation by the IE. The IE will again assess the participants upon termination of treatment. Participants will then enter the non-treatment follow-up phase. Participants who prematurely terminate therapy (before 70% symptom reduction or 7 sessions) will undergo a post-last session assessment with the IE and will then enter the follow-up phase. Follow-up assessments will be conducted at 3-, 6-, and 12 months post-treatment and annually thereafter. The IE assessments will comprise both structured clinical interviews and self-report measures. The assessments will cover PTSD severity, related psychopathology, general psychopathology, and PTSD-related cognitions. At the 12-month follow-up, participants who receive SC and are deemed to still have clinically significant PTSD symptoms (as determined by the IE at 12-month follow-up assessment), will be offered PE-A. To add to the rigor of the study and demonstrate the long-term efficacy of the intervention, there will be annual posttreatment follow ups, dependent on the availability of funds for this purpose.

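### The protocol gives two times for offering PE-A to symptomatic SC participants; the earlier one would mix treatments in the SC arm at the 3-, 6- and 12-month visits

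*Protocol article*

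**What the plan says.** Two sections of the protocol article describe an offer of PE-A to participants randomised to SC.

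- Method, *Design*: "At the 12-month follow-up, participants who receive SC and are deemed to still have clinically significant PTSD symptoms", with the independent evaluator (IE) as judge at the "12-month follow-up assessment), will be offered PE-A".
- Discussion, *Protection against risks*: SC participants who keep a PTSD diagnosis or "manifest significant trauma-related symptoms, will be offered PE-A at the end of treatment".

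The period between those two times is described twice. In *Design*, after the assessment at the end of treatment, "Participants will then enter the non-treatment follow-up phase". In *Potential risks*, "all participants are exposed to the risk of relapse during the non-treatment follow-up". The schedule is in *Design*: "Follow-up assessments will be conducted at 3-, 6-, and 12 months post-treatment and annually thereafter".

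The between-arm claim under *Research hypothesis* is that PE-A will be superior to SC "in reducing PTSD symptoms at post-treatment as measured by the Child PTSD Symptom Scale". The follow-up claim is that "PE-A treatment gains will be maintained at 3-, 6-, and 12-month follow-up and annually thereafter". *General considerations for data analysis* lists the pre-, mid- and post-treatment, follow-up and annual assessments as the repeated measures. It then examines treatment difference with a linear mixed model (LMM) as the main tool and GEE as a robustness check.

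**The concern.** Staff cannot follow both texts, and families could be told either. The choice decides what some SC participants receive during the first year after treatment.

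It also decides what the SC arm represents at 3, 6 and 12 months. Under the 12-month offer, SC at those visits is SC alone. Under the end-of-treatment offer, SC participants who still have symptoms could have begun PE-A by then. Crossover would depend on outcome and go in one direction, so a between-arm estimate at those visits would no longer describe PE-A against SC alone.

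**Working it through.** The plan states no figure on this point, so the check compares the texts and then gives an illustration.

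**1. Can the two times be the same?** No. *Design* fixes the order: treatment ends, the IE assesses, follow-up begins, and visits follow at 3, 6 and 12 months after treatment. The end of treatment and the 12-month visit are therefore about a year apart.

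**2. Could both offers be intended, one after the other?** Neither section mentions the other. An offer accepted at the end of treatment would also put PE-A inside a period that *Design* and *Potential risks* both describe as free of treatment.

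**3. Are the criteria the same?** They overlap but differ. *Design* uses clinically significant PTSD symptoms and names the IE as judge. *Protection against risks* uses a retained diagnosis or, more widely, significant trauma-related symptoms, and names no judge.

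**4. What is affected?**

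| Comparison | Offer at 12 months | Offer at end of treatment |
|---|---|---|
| PE-A v SC, post-treatment (primary) | unaffected | unaffected if rated before the offer |
| Maintenance within PE-A | unaffected | unaffected |
| PE-A v SC, 3 and 6 months | SC alone | SC alone mixed with SC then PE-A |
| PE-A v SC, 12 months | SC alone if rated before the offer | mixture |
| PE-A v SC, annual visits | mixture, by open design | mixture |

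The two texts differ in effect at 3, 6 and 12 months.

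**5. Illustration of size.** None of these quantities is in the document. At a given visit let:

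- δ = mean CPSS-I under SC alone minus mean under PE-A (δ > 0 if PE-A is better);
- c = share of the whole SC arm that has taken PE-A by that visit;
- g = mean reduction those participants gain from it.

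The SC mean falls by c × g, so the observed contrast is δ − c·g, which is a fraction 1 − c·g/δ of δ.

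| c | g = δ | g = δ/2 |
|---|---|---|
| 0.20 | 80% | 90% |
| 0.40 | 60% | 80% |
| 0.60 | 40% | 70% |

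With g = δ the fraction is simply 1 − c. The contrast moves towards zero whenever g is positive and c·g does not exceed δ. PE-A takes 7 to 14 weekly sessions, so a participant who crosses over at once could still be in treatment at 3 months (about 13 weeks). The effect there could be smaller than at 6 and 12 months.

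**The case against.** The strongest reply is that little of the trial's stated purpose depends on this. The superiority hypothesis is tested at post-treatment, and *Design* places that assessment before follow-up begins. The follow-up hypotheses and objectives all concern maintenance of PE-A gains, and none states a between-arm difference at 3, 6 or 12 months. This stands, and it limits the severity.

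Three further replies also stand. Crossover after the 12-month visit is an openly stated design feature. The handling of data after crossover may be set out in an analysis plan that is not shown, so its absence here is no fault. The two criteria overlap heavily, so the difference in wording is minor beside the difference in timing.

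These replies do not remove the contradiction. The LMM and GEE are described over all assessments, so between-arm estimates at follow-up can be expected. An analysis plan can choose how to treat crossover, but it cannot undo crossover that has already happened.

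A reader might infer more than the text supports, in three ways.

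- *That the SC arm would have no untreated follow-up.* The earlier version is an offer, and only to symptomatic participants. SC responders and those who decline would remain untreated.
- *That power at follow-up would fall from 80% to about a third.* With 32 completers per arm and two-sided alpha 0.10, 80% power implies d = (1.645 + 0.842) × √(2/32) = 0.622. Halving it (c = 0.5, g = δ) gives 0.311, a noncentrality of 0.311 × √16 = 1.24, and power of about 34%. The arithmetic is right, but *Sample size* states no d, refers to effects within each group, and ties its 80% to no follow-up visit. The crossover share is also assumed. The protocol never claimed the power that this would take away.
- *That crossover of only the worst cases must shrink the contrast further.* That holds only if those cases gain more than the average arm difference (g > δ).

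**Conclusion.** The contradiction is real: two current texts set offer times about a year apart with different criteria, nothing reconciles them, and the earlier one conflicts with the description of follow-up as untreated.

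The statistical consequence is conditional. It arises only if the end-of-treatment text is followed and symptomatic SC participants accept. The between-arm estimates at 3, 6 and 12 months would then compare PE-A with SC plus optional PE-A, probably biased towards no difference. The size cannot be given from the document; the 1 − c fraction is an illustration that assumes both uptake and full benefit. The primary post-treatment comparison is unaffected provided its rating comes before the offer, and the statement about maintenance within PE-A is also unaffected. Should-fix. No view is taken on which offer time is clinically right.

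**What to change.** 1. Reconcile *Design* and *Protection against risks* to one offer time, one criterion and one named judge, chosen by the clinical team. Align the descriptions of the follow-up phase in *Design* and *Potential risks* with that choice.
2. State that the CPSS-I rating at the visit where the offer is made is completed before any offer.
3. Record the PE-A start date for every SC participant who takes up the offer.
4. State that between-arm estimates at visits after the offer describe SC with optional later PE-A, not SC alone. Do not simply exclude outcomes after crossover: uptake depends on outcome, so exclusion would selectively remove poor SC responders and could itself introduce bias.

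The cost is a few sentences of protocol text and one date field. If offers have already been made, the rule actually applied and the start dates should be recovered from the treatment records.

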### Ethics approval

This study has been approved by the Health Research Ethics Committee at Stellenbosch University (N12/06/031) and will be conducted according to the ethical guidelines and principles of the international Declaration of Helsinki, South African Guidelines for Good Clinical Practice and the Medical Research Council (MRC) Ethical Guidelines for Research.

Permission was also obtained from the Western Cape Education Department (WCED) to offer treatment at the participants’ schools. Permission from the WCED was conditional on not disclosing the identities of the participating schools.

Consent will be obtained from parents of potential participants in the study. Informed consent and assent will be obtained by the IE when determining eligibility and prior to randomization to treatment. A participant may leave the study at any time. Study procedures as well as potential risks, benefits and treatment alternatives will be explained at the time participation in the study is discussed. Participants will be clearly informed of the voluntary nature of their participation and their right to terminate without any penalty.

The one IE, an experienced Clinical Psychologist, will screen participants for other psychopathology and will not include a potential participant if the principal diagnosis is not PTSD in response to a traumatic event.

Participating schools’ headmasters and educators will be informed that the study entails the treatment of adolescents that have experienced a trauma. In this way adolescents will not be identified in terms of the nature of their trauma. Counsellors will keep all study and personal information about participants confidential.

Participants will receive all written material in their language of choice (Afrikaans, English and Xhosa).

All counsellors will receive weekly supervision, on every participant under their care. Counsellors will have unrestricted access to the supervisor. Participants in both PE-A and SC will be informed that they can contact their counsellor between sessions should they experience a crisis or are distressed enough to need support. If a counsellor is concerned about a participant’s psychological welfare, the supervisor will arrange for a psychological assessment. Although unlikely, should significant negative emotional reactions develop that require other forms of intervention, the participant will be withdrawn from the study and will be appropriately referred.

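### Safety withdrawals are taken out of the study rather than out of treatment, and the article does not say whether the rule for early stoppers still collects their CPSS-I (minor wording fix)

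*Protocol article*

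**What the plan says.** All references are to the protocol article.

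**Early stoppers (Design, text after Fig. 1).** "Participants who prematurely terminate therapy (before 70% symptom reduction or 7 sessions) will undergo a post-last session assessment with the IE", after which they enter the follow-up phase. No reason for stopping is excluded. The schedule is then general: "Follow-up assessments will be conducted at 3-, 6-, and 12 months post-treatment and annually thereafter".

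**Safety cases.**
- Ethics approval: for significant negative emotional reactions that need another form of intervention, "the participant will be withdrawn from the study and will be appropriately referred".
- Protection against risks: "if substantial negative emotional reactions develop that require additional interventions, participants will be withdrawn from the study and referred" to public services.
- Protection against risks, on acute danger: "In cases where danger to self or others is identified, the adolescent will be withdrawn from the study", and emergency procedures follow.

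**Safeguards.** When a counsellor is worried about a participant, "contact will be made with the supervisor and PI who will arrange for psychological evaluation". Independent evaluators as well as counsellors may identify such cases, in consultation with the principal investigator. A DSMB meets every 6 months. Reactions that need added intervention are described as unlikely, and no rate is given.

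**Outcome and analysis.** The primary outcome is the CPSS-I total score rated by the independent evaluator, at post-treatment and then for maintenance at follow-up. The main analysis is a linear mixed model with GEE as a robustness check, and both are said to accommodate missing data.

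**The concern.** An adolescent removed for safety at, say, session 4 has stopped therapy before session 7 and has also been withdrawn from the study. The first fact calls for a closing CPSS-I and follow-up. The second, taken at its word, calls for neither.

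These adolescents leave because they are doing badly. A missing score would then probably depend on the score itself, beyond what earlier visits explain. A likelihood-based mixed model corrects for loss that the observed scores explain, but not fully for this kind. GEE needs assumptions at least as strong. No later analysis can recover a score that was not taken. The loss could also differ by arm, since only PE-A uses exposure, although the article gives no evidence that it would.

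**Working it through.** **1. The wording side by side.** The Design rule concerns stopping therapy. The safety rules concern leaving the study. Three features suggest that the second term is not simply shorthand for the first:
- Ethics approval also says "A participant may leave the study at any time", where the study naturally means all participation.
- The relevant part of Protection against risks opens with participants' "reactions to study assessments and treatment will be closely monitored, and negative reactions will be addressed therapeutically", so it names assessments and treatment as separate things.
- Independent evaluators may identify these cases, and they also see participants at 3, 6 and 12 months, when study treatment is over. For a case identified then, withdrawal from the study could only mean an end to assessments.

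No sentence says outright that CPSS-I collection stops, and none says which rule prevails.

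**2. The only related figure in the plan.** Sample size states 30% dropout, 90 entrants and 64 completers. Check: 90 × 0.70 = 63, and 64 / 0.70 = 91.4, so 92. Both agree with the stated figures to within two participants. The point does not rest on them.

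**3. Possible size, under assumptions.** No withdrawal rate is given, so the inputs below are assumed, apart from the 45 per arm:
- a fraction p of one arm is lost, 1/45 or 2/45;
- those lost are the top p on a selection score that correlates s with the post-treatment CPSS-I, s from 0.5 to 1.0;
- mid-treatment and post-treatment scores correlate r, from 0.4 to 0.7, and the model uses the mid-treatment score.

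With standardised normal scores, z the upper-p normal quantile and φ its density, the retained mean is too low by s·φ(z)/(1 − p). Adjustment for the mid-treatment score removes about r² of that:

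bias ≈ s × φ(z)/(1 − p) × (1 − r²)

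- p = 1/45: z = 2.010, φ = 0.0529, φ/(1 − p) = 0.0541. Smallest: 0.5 × 0.0541 × 0.51 = 0.014. Largest: 1.0 × 0.0541 × 0.84 = 0.045.
- p = 2/45: z = 1.701, φ = 0.0938, φ/(1 − p) = 0.0982. Smallest: 0.5 × 0.0982 × 0.51 = 0.025. Largest: 1.0 × 0.0982 × 0.84 = 0.082.

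Simulation does not need the approximation and agrees closely:

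| Loss | Bias in the contrast (SD) |
|---|---|
| 1 of 45, one arm only | 0.014 to 0.046 |
| 2 of 45, one arm only | 0.025 to 0.085 |
| 2 in one arm, 1 in the other | 0.012 to 0.039 |
| 1 in each arm | 0.000 |

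If withdrawal comes before the mid-treatment visit, only the baseline score helps. With an assumed correlation of 0.2 to 0.4, the ranges become 0.023 to 0.052 for one lost and 0.041 to 0.095 for two.

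**4. Scale.** The article states no effect size. For a two-sample t-test with 32 per arm, two-sided alpha 0.1 and 80% power, the detectable difference is about 0.63 SD. This is a back-calculation for comparison only, since the planned analysis is a mixed model.

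**The case against.** **The two rules can be reconciled.** Sample size equates premature termination with dropping out, so the Design rule may be meant for adolescents who stop of their own accord. The safety text would then be a specific exception imposed by the team. Alternatively, the Design rule may cover everyone who stops early, and nothing is lost. This stands: it would be too strong to infer a flat contradiction, or to infer that the plan orders CPSS-I collection to stop. What remains is that the two readings give opposite instructions on the primary outcome, and the text does not choose.

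**This is detail for the full protocol.** In part. A condensed article need not spell out procedures after withdrawal. But here the article does state a rule, and its literal wording goes further than ending treatment. That is more than silence.

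**Ending participation may be a deliberate protective choice.** This is reasonable. Potential risks names interviews and questionnaires as sources of discomfort, and the article separately allows discretion after a social work referral. Any fix must therefore let clinicians waive assessment. The most severe cases are the likeliest to be waived, so only part of the data would be kept.

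**The larger figures are corner cases.** This also stands. The top of the range needs two losses in one arm and none in the other, selection tied perfectly to outcome, and a weak correlation with earlier scores. A reader might infer a material loss of power or an inflated type I error. The document does not support that: it gives no rate and no sign of loss in one arm only, and the 30% allowance for dropout (27 of 90) is far larger than one or two safety cases.

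**Conclusion.** The point holds as a minor ambiguity that is cheap to remove. Taken literally, the safety wording ends primary-outcome collection for an outcome-related reason, while the Design section keeps collecting after therapy stops early, and the article does not say which applies.

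Its size cannot be derived from the document. Under the assumptions above, the bias is about 0.01 to 0.09 SD when one or two of 45 are lost from one arm only (0.095 at most if they leave before mid-treatment), and near zero when loss is equal. The direction is unknown. Scores taken before withdrawal stay in the model, and the DSMB reviews safety and data integrity. The design and the stated sample size are not called into question.

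**What to change.** In Ethics approval and in both places under Protection against risks, write that the participant is withdrawn from study treatment and referred, and that the assessment and follow-up rule in the Design section still applies. Leave referral, clinical decisions and emergency procedures unchanged. Offer at least the CPSS-I, listed at 10 minutes in Table 3, after the last session and at the planned follow-ups. Waive it if consent or assent is withdrawn or the clinical team judges assessment harmful. Say that the same applies to a case identified during follow-up.

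Cost: a few sentences, and a few short evaluator contacts on visits already scheduled. There are two downsides. A few distressed adolescents carry a short assessment burden, which the waiver limits. Their later scores will also include the effect of referred care, so the contrast becomes that of the assigned treatment together with whatever care followed.
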